### Recruitment and consent

The current evaluation will employ various recruitment strategies, with consent procedures tailored to each data collection activity. The implementation of Safe Steps follows an opt-in model, with recruitment proceeding through an asynchronous, multi-centre approach [65]. Each site independently decides when to implement Safe Steps, allowing for autonomy and flexibility, while ensuring consistency in the intended intervention across settings. Recruitment began at the first intervention site on 1st March 2024, with the latest site starting on 16th April 2024. Baseline data collection for the unit register, ims+, and eMeds data, covering the year before each site’s recruitment start date, commenced alongside recruitment. The final recruitment and data collection will conclude one year after the latest recruitment start, on 15th April 2025. At the time of the initial submission of the protocol for publication consideration, the study has reached its third time point.

For event-based analyses, the consent to access administrative data from unit registers and incident management systems was waived, because individual and nurse participant identifiers will not be gathered, nor will the data be re-identifiable. On the other hand, completion of the de-escalation log will serve as implied consent, and no identifying nurse details will be recorded. Identifying individual information will be gathered solely to help complete the logs, after which it will be removed and replaced with a randomly assigned study code before being shared with the first author.

For survey-based measures, peer worker-led surveys will be open to individuals over 18 who can consent to participate in the research. The only exclusion criteria are individuals receiving care with an identified need for an interpreter who refuse to use interpretation services adjacent to the unit. Increasing access to research participation with interpretation services was done with the consideration of guidance from the state-wide service that streamlines care pathways for culturally and linguistically diverse (CALD) individuals.

Each individual admitted to the intervention sites during data collection will receive a participant information sheet (PIS). Before discharge, people receiving care who meet the inclusion criteria will be approached by a peer worker and a nurse and provided with another copy of the PIS. To bring decision-making as close to the individual participant as possible, a nurse will assess an individual participant’s capacity to consent through the modified version of the University of California, San Diego Brief Assessment of Capacity to Consent [66]. Individual participants will be able to express interest in an interview through the final survey question, with identifying details quarantined from survey responses. Where needed, interpreters will be asked to support CALD participants during the capacity-to-consent assessment, survey completion, and interviews.

For the qualitative strand, nurses at intervention sites will be informed of the study during staff meetings and invited to participate in surveys and focus groups. They will receive the PIS and an email with a survey link. Focus group discussion recruitment will include information sessions, and nurses will be notified of focus group discussion timings via email. Written consent will be obtained before participation in focus group discussions. In contrast, nurses can indicate their consent through an item on the online survey.

### Measures

A battery of researcher-made and adapted standardised measures will be utilised in the evaluation. Adaptation was based on the context of acute mental health services and the research aims in which the evaluation occurs. Explicit permission was obtained for using and adapting the standardised measures, particularly those not openly available to the public. Best practice guidelines on psychometric validation of standardised measures will be followed [67,68].

#### Mental health nursing de-escalation logs.

The mental health nursing de-escalation log developed by a clinician (MF) in collaboration with another clinician (AT) has five sections: i) incident details, ii) aggression type, iii) interventions, iv) situational aggression levels, and v) outcomes, covering 51 variables. It records contextual information (date, location, number of staff involved), direction of aggression (e.g., individual to nurse), and lists interventions like the four Safe Steps and other non-relational, non-coercive de-escalation techniques. Situational aggression levels are rated on a 6-point scale from calm to physical aggression with weapons. Outcomes include restrictive practice use (e.g., seclusion, physical restraint, sedation via intramuscular injections), Code Black, time out, care level allocation, physical injuries, and incident management system reporting. Nurses will be trained to complete these logs, which they will contemporaneously cross-reference with unit data to minimise recall bias. Concurrent validation of the restrictive practice use outcomes will be attempted.

#### Fidelity checklist.

This checklist is an adaptation of the observational measure used in evaluating the implementation of the Safewards [20]. The adaptation concurs with the Safe Steps intervention and outcomes gathered through the de-escalation logs. Items 1–5 align with the implementation checks on the components of the Safe Steps, and items 6–10 are on the specific outcomes captured by the logs. There are no established norms that define full or partial implementation. However, the authors will consider higher scores on the first five items to indicate more vigorous implementation. In comparison, lower scores on the first five items suggest partial or minimal implementation.

#### Nurses survey.

The nurses in the intervention sites will be offered the opportunity to complete an online survey. The survey includes an introduction to the research and access to a PIS. After confirming their consent, participants will complete nine items of the Short Professional Quality of Life Scale [Short ProQOL; [71,72]; The Center for Victims of Torture, 2021; see www.ProQOL.org] and 70 items of the Genos Emotional Intelligence Inventory [73]. The study will collect demographic information through direct questioning. The demographic information will be reported as summaries, but not included in the primary data analysis. Finally, the survey concludes with a page where nurse participants can provide their e-mail addresses to gain an individualised emotionally intelligent workplace behaviour self-report. Only scores from the concise version (31 items) of the emotional intelligence inventory will be analysed for the Safe Steps evaluation. The scoring and interpretation of the standardised measures will follow their intended design and guidelines. Internal reliability estimation and factor structure validation of the standardised measures will be attempted.

#### Semi-structured interview schedule.

A researcher-made semi-structured interview schedule will be used with six main questions about admission, demographic information, ward experience, person-nurse relationships, restrictive practices experiences, and nurse actions.

#### Focus group discussion prompt.

A researcher-made focus group discussion prompt will be used with five main sections on individual aggression and emotional distress responses, individual relationships, needed de-escalation competencies, intervention implementation, and emotional intelligence.

### Procedures

The participating nurses will receive the training programme component of the Safe Steps. Nurse educators will support the opt-in-based implementation of the three components of the Safe Steps, ensuring that it is an integrated aspect of everyday practice in providing acute mental health care. Regular meetings, site visits, posters on the intervention’s key values, pull-up banners, coffee vouchers, and cheat sheet cards on the four steps will be implemented to support intervention uptake. Changes in nursing practices and measures of individual and nurse participants’ outcomes and experiences in the intervention sites will be collected over two years at various time points (see Fig 2). Restrictive practice and physical injury outcomes will be gathered prospectively from both intervention sites and control groups from administrative records, except for the de-escalation log. Outcomes from standardised measures and qualitative data will be collected prospectively only from people receiving care and nurse participants in the intervention sites. Data collection may cease due to unforeseen circumstances, such as reinstated COVID-19 restrictions.

### Analysis plan

Quantitative and qualitative analyses will be used to answer the evaluation’s objectives. Consultations with statisticians occurred for the range of statistical treatments employed in this evaluation. Various packages in R [74] and RStudio [60] will be maximised for the quantitative analyses, and Matplotlib [75] will be utilised for visualising outcomes. Each hypothesis will be supported if outcomes are statistically significant at p < .05.

Poisson mixed-effects models [56] will be used for count data and linear regression models for continuous outcomes, to determine whether these outcomes differ according to intervention implementation and time points. Data cleaning and validation, assumption checks, model diagnostics, and follow-up analyses will be undertaken. Negative binomial mixed models, zero-inflated models, and linear mixed-effect models may be used depending on the model’s diagnostics. Covariates in the mixed-effect models will include the acute care unit, calendar month, day, year, and the day within the study period for each daily event aggregate. Model selection will prioritise parsimony and explanatory strength. Inverse probability weighting (IPW) will be applied in the between- and within-group comparisons. Using the ipw package [76], IPW will be used to balance covariates, including but not limited to the average harm scores of daily aggregates, the number of high observation beds, the number of seclusion rooms, and other confounds (i.e., physical restraint and Code Blacks are closely interrelated, influencing each other’s occurrence or implementation [77]). Listed covariates for balancing will be used, subject to the data’s fit and the statistical model’s ability to achieve convergence in the IPW approach.

Hierarchical clustering analysis [78] will support the emergence of co-occurring mental health nursing response clusters, which will then be the fixed effect in modelling differential associations with restrictive practices, physical injuries, and situational aggression. This cluster and regression analysis constitutes the between-cluster comparison to identify the most active response clusters contributing most to Safe Steps’ overall impact.

Given the quality checks associated with national key performance indicators for mental health services, there is no expected missing data for the primary outcomes. However, log data may undergo multiple imputations under different missing data mechanisms [79] to minimise bias due to missing data. A day without log data will contribute to the missingness rate. Lastly, fidelity scores will be described statistically and plotted in a graph.

For survey-based measures, a one-way analysis of variance will be used to assess differences over time in people measures. In contrast, a paired t-test will examine changes in nurses’ measures over time. Missing data of not more than 20% will be imputed using multiple imputations [80]. Measures with less than 80% of the total items completed will be excluded. Non-parametric statistical models may be used if distributional assumptions are violated.

For the qualitative strand, pluses and wishes, transcribed interview responses, and focus group discussion data, will be analysed using NVivo 12 Pro software [81] and alternatively through a spreadsheet. An analytical process [82,83] that involves re-reading transcriptions for familiarisation, organising data, coding and condensed coding, and refining thematic results through a team approach, will be systematically led by the first author to integrate multiple perspectives. A codebook will be maintained [84]. Individual participants can review their responses for accuracy before analysis [85].

Machine learning techniques, including but not limited to random forest [86] and Boruta algorithm [87], will be maximised to undertake a feature analysis on the most important drivers of aggression and restrictive practice use. Qualitative log responses on triggers of de-escalation will be coded and considered in feature analyses.

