**Fig 2 pone.0325558.g002:**
[figure not shown]
Outcomes and data gathering timeline. CEO-MHS = Consumer Evaluation of Mental Health Services; EI = emotional intelligence; eMeds = electronic medication management system; IMI = intramuscular injection; ims+ = incident management system; ProQOL = Professional Quality of Life; VPC-M-FR = Modified Violence Prevention Climate.

There will be three forms of comparisons within the current evaluation. Between- i) and within-group ii) comparisons will be applied to test the first and second sets of hypotheses. The third will be a between-cluster comparison iii), intended to identify the most active co-occurring therapeutic and nursing responses (clusters) contributing to the Safe Steps’ overall impact. The first set of hypotheses is that implementation units will exhibit greater reductions in the IRR for restrictive practice events, the estimate of restrictive practice duration, and the IRR for physical injuries, compared to control groups and their baseline levels. The second set of hypotheses is that measures of service experience, perceived staff action towards violence prevention, nurses’ professional quality of life, and nurses’ perceived demonstration of emotionally intelligent workplace behaviours at the final time point would be significantly higher than at baseline. The between-group comparisons will be conducted exclusively to address the first objective, as these analyses will depend on accessible routine reports on restrictive practices and physical injuries selected for this purpose. Australian public acute mental health services are legally mandated to report on seclusion and physical restraint events and duration as key performance indicators [52]. Events of physical injuries and sedation via IMI are also routinely documented in established information management systems. These routine measures will help minimise performance and detection bias associated with the lack of blinding. Conversely, conducting a between-group comparison on non-routine measures could be cost-prohibitive and challenging to implement, as exemplified by unmet sample size requirements in previous studies [27]. This evaluation will have no randomisation, although covariate balancing will be applied to between- and within-group comparisons in testing the first set of hypotheses.

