### Setting

The evaluation will be conducted across two NSW local health districts (LHDs). LHDs in NSW are health administrative regions with distinct budgets and governance under Australia’s universal healthcare framework, making up geographically based districts and three specialised networks. The intervention sites will consist of three declared adult mental health inpatient units, with a combined capacity of 75 beds, including ten designated for high observation. Operating 24 hours a day and situated within public hospitals, these units cater to varying levels of mental health treatment and observational needs. Delivering acute care from these units to people from different catchments and adjacent local government areas are peer workers and traditional staff from different disciplines, including but not limited to nurses and nurse educators. These units vary in local care models, restrictive practice rates, peer work involvement, and restrictive practice review approaches.

The control sites will be three declared adult inpatient units within two public hospitals in one LHD. Their total bed capacity is 84, and they are without high observation areas. Clinical input supported identifying these sites, considering the bed capacity and availability of high observation beds. One control site has no seclusion room, making it impossible to observe seclusion events or measure their duration. However, as detailed in the Analysis Plan section, the number of seclusion rooms and high observation beds will be considered for covariate balancing. Similar to the intervention sites, the three control units operate with varying levels of mental health practices and are multidisciplinary.

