### Sample

Outcome change measurement and qualitative research within the evaluation depend on two forms of samples: daily aggregates of observed events and individual and nurse participants. Daily aggregates of restrictive practice and physical injury events will be used to analyse these outcomes. In contrast to a ‘per incident’ level, an aggregated approach helps prevent the false impression of completeness [20]. It enables a more accurate evaluation of potential reporting biases in real-world data. On the other hand, people receiving care and nurse participants will be involved in the qualitative strand and survey-based measures.

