### Sample size

The sample size for this evaluation was determined using a combination of power analyses, prior research findings, and feasibility considerations. Both quantitative and qualitative approaches were employed.

For event-based analyses, Monte Carlo simulations using the simr package [59] and RStudio [60], were used to estimate the necessary duration of data collection. A Poisson mixed-effects model was applied to synthetic data replicating the initial implementation outcome parameters. To detect a 12% reduction in seclusion rates with 99.30% power, at least 3.60 months of data collection is required. To identify significant changes in physical restraint incidents, a 12-month period is necessary to achieve 90.60% power. In comparison, 10.8 months are required to detect differences in Code Black/ Assist events with 85.20% power. These calculations include a 20% buffer to account for potential attrition and were conducted with an alpha level of 0.50, aligning effect size assumptions with findings from the NSW Safewards evaluation [61]. The NSW Safewards evaluation was chosen as a reference, due to its high methodological quality and relevance to the same geographic and service context as this evaluation, being the only study identified in an overview of systematic reviews with such characteristics [5].

For survey-based measures, sample size estimations were conducted using G*Power 3 [62]. Based on power calculations, a minimum of 135 individual survey responses is required across intervention sites, incorporating a 30% margin for potential exclusions to achieve 95% power. Similarly, a minimum of 60 nurse surveys is necessary, maintaining the same power assumptions and buffer levels.

For the qualitative component, data will be collected through semi-structured interviews and focus groups. At least 15 individual interviews will be conducted at T2 and T4, with additional interviews, if necessary, until data saturation is reached. Additionally, three to five focus group discussions will be conducted per site, including six nurses involved in intervention implementation since baseline. These sample size decisions are informed by systematic reviews on qualitative research methodologies, indicating that such numbers are typically sufficient to achieve thematic saturation in studies using interviews [63] or focus groups [64].

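### The stated models for daily event counts include no measure of occupied beds, so a unit-specific change in occupancy can be read as, or can hide, an intervention effect

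*Protocol article*

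**What the plan says.** The Sample section sets the unit of analysis: "Daily aggregates of restrictive practice and physical injury events will be used to analyse these outcomes". The first set of hypotheses (Design section, text after Fig 2) is stated on the rate-ratio scale: "implementation units will exhibit greater reductions in the IRR for restrictive practice events". It covers comparison both with controls and with the units' own baseline.

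Under Analysis plan, "Poisson mixed-effects models [56] will be used for count data and linear regression models for continuous outcomes", with negative binomial and zero-inflated alternatives if diagnostics call for them. The model terms follow: "Covariates in the mixed-effect models will include the acute care unit, calendar month, day, year, and the day within the study period". The next sentence adds "Model selection will prioritise parsimony and explanatory strength". The covariates named for inverse probability weighting are harm scores, high observation beds, seclusion rooms and related confounds such as restraint and Code Blacks. That list is expressly left open.

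Bed numbers appear in the Setting section only. The intervention units are described "with a combined capacity of 75 beds, including ten designated for high observation". For the control units, "Their total bed capacity is 84, and they are without high observation areas". Capacity is mentioned as a consideration in choosing control sites. Occupied beds, bed-days, admissions, an exposure term and an offset are not mentioned anywhere.

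**The concern.** A daily count on an inpatient unit depends on how many people are on the unit and on the risk each of them carries. Safe Steps is meant to change the second. With one row per unit-day and no occupancy term, the fitted IRR compares events per unit-day and mixes the two.

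Part of this is dealt with. The unit term removes fixed size differences, so 75 against 84 beds is not itself a problem. The month, year and study-day terms remove drift common to all six units. What remains is change specific to some units over the two-year window, such as a bed closure, a surge or a gradual drift in occupancy. High observation beds and seclusion rooms describe a unit's facilities and do not track its daily census.

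With three units per group, a change in one or two units can move the between-group contrast. The within-group comparison has less protection. It has no concurrent control, and the intervention units started between 1 March and 16 April 2024, so calendar terms separate only partly from the intervention period. An occupancy change at about that time would be hard to tell from an effect.

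**Working it through.** **The plan's own figure.** The effect size available as a yardstick is in the Sample size section: "To detect a 12% reduction in seclusion rates with 99.30% power", from 3.60 months of data. The power cannot be reproduced because neither baseline event rates nor variance components are given. A simple two-rate Poisson approximation, E = (z for alpha/2 + z for power)² × (1 + 1/RR) / (ln RR)², with RR = 0.88 and alpha 0.05, gives (1.960 + 2.457)² × 2.136 / 0.01634, or about 2,551 baseline events. The simulation's real inputs are unknown, so this does not show the figure to be wrong. Only the 12% (rate ratio 0.88) is used below.

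**Inputs from the document.** Three intervention units with 75 beds in total; three control units with 84; one year before and one year after the start; daily counts; IRR; two-sided p < .05.

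**Inputs assumed.** Occupancy levels, the size and timing of any change, and event rates. The document gives none of these.

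**Bias in the IRR.** If events are proportional to occupied beds and control occupancy is stable, then without an occupancy term:

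fitted IRR = true IRR × (occupied beds after / occupied beds before)

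With a true IRR of 1:

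- 95% to 90%: 0.90/0.95 = 0.947, a fall of 5.3%, or 5.3/12 = 44% of the target.
- 95% to 85%: 0.85/0.95 = 0.895, a fall of 10.5%, or 10.5/12 = 88% of the target.
- 9 fewer occupied beds, taking 75 as occupied before: 66/75 = 0.880, the whole target.

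In the other direction, with a true IRR of 0.88:

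- 90% to 95%: 0.88 × 0.95/0.90 = 0.929.
- 85% to 95%: 0.88 × 0.95/0.85 = 0.984, so the effect almost disappears.

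**False-positive rate.** Simulated Poisson counts, no true effect, 25 beds in each intervention unit and 28 in each control unit, 92% occupancy at the start, 365 days before and after. The model had unit, month, period and group-by-period terms, with 400 runs per setting. Occupied beds fall in the intervention units only.

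| Events per occupied bed-day | Fall in occupied beds | IRR, no occupancy term | Rejected at p < .05 | IRR, log-occupancy offset | Rejected at p < .05 |
|---|---|---|---|---|---|
| 0.01 | 0% | 0.997 | 4.5% | 0.997 | 4.5% |
| 0.01 | 5% | 0.949 | 7.3% | 0.999 | 3.8% |
| 0.01 | 10% | 0.905 | 13.3% | 1.005 | 6.3% |
| 0.02 | 0% | 1.006 | 5.0% | 1.006 | 5.0% |
| 0.02 | 5% | 0.949 | 7.3% | 0.999 | 4.3% |
| 0.02 | 10% | 0.896 | 24.8% | 0.996 | 4.8% |
| 0.04 | 0% | 1.003 | 6.5% | 1.003 | 6.5% |
| 0.04 | 5% | 0.944 | 16.8% | 0.994 | 4.0% |
| 0.04 | 10% | 0.897 | 41.0% | 0.997 | 5.8% |

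With 400 runs, the standard error of a 5% rejection rate is √(0.05 × 0.95/400) = 1.1 percentage points, so the offset columns are consistent with 5%. The simulation has no weighting, random effects or study-day term. It shows the mechanism and does not estimate this study's error rate.

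**The case against.** The strongest reply is that this is a condensed article, an offset is a routine specification detail, and an offset is not a covariate, so a list of covariates does not exclude one. That is fair. The text is silent on an offset and does not forbid it. A reader might infer from the list that the model is closed and occupancy ruled out. The document does not support that: the list is not declared final, model selection follows it, and the weighting list is open.

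A reader might also infer that the IRR has no denominator. It has one, the unit-day, and a rate ratio per unit-day is a legitimate quantity. Events per occupied bed-day is a different target. The point is that the second target isolates the risk the intervention is meant to change, while the first also moves with occupancy.

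Third, no occupancy change is documented, and in the between-group comparison only a differential change matters. This stands, and it makes the bias conditional. It is also true that the smaller illustrated change, 95% to 90%, reaches less than half of the target. The larger one would have to hold across the intervention units for the whole follow-up year. Moreover, the 12% is printed for seclusion only.

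Finally, an offset forces events to be exactly proportional to occupied beds. Seclusion also depends on seclusion rooms, and one control site has none. Proportionality should therefore be checked, which the fix below provides for.

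None of these points removes the gap. The terms that are named leave unit-specific occupancy change uncontrolled, and a simple addition controls it.

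**Conclusion.** The point holds as a worthwhile and inexpensive improvement to the stated model. The named model and weighting covariates contain no measure of occupied beds, so a unit-specific change in occupancy between baseline and follow-up can imitate or mask an effect. The within-group comparison is the most exposed.

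For size, a differential fall from 95% to 90% produces an apparent 5.3% reduction with no true effect, and a fall from 95% to 85% produces 10.5%, against a planned 12% for seclusion. These figures rest on assumed occupancy, stable controls and events proportional to occupied beds. The false-positive rates rest also on assumed event rates. A reader might go further and infer that the results will be biased. The documents do not support that, because they contain no occupancy data.

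**What to change.** Obtain the daily census for the six units over the baseline and follow-up years. Include log occupied beds as an offset in the daily count models, both between and within groups, and report IRRs per occupied bed-day.

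Add two sensitivity analyses:

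- Enter log occupied beds as a covariate with a free coefficient. A coefficient far from 1 means that proportionality fails and the offset result should be read with caution.
- Fit the unit-day count without any occupancy term, so that readers see how much the denominator matters.

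The cost is a few sentences in the analysis plan and one further administrative data request to units that already supply such records. Recruitment, intervention and outcome collection are unchanged.
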